## Methods/Design

### Participants

174 female adolescents aged 10.0 to 13.0 years were recruited from the community, together with one of their parents/guardians. See **Table 1** for a list of exclusion and inclusion criteria. Families were recruited primarily through recruitment letters distributed by schools in the greater Eugene/Springfield area (Lane County, Oregon, USA), and to a minimal extent from secure databases of people who registered their interest in our lab's/department's research, recruitment flyers posted around the community or disseminated at community events, and through snow-balling efforts. Recruitment letters were sent to families with children in grade 5 or 6 that were registered as female by the schools. Initially, 189 participants were recruited, but 7 of them failed to meet inclusion/exclusion criteria and another 8 withdrew before completing Time 1 assessments, leading to 174 participants at Time 1 of the study. Parents/guardians have given written informed consent and adolescents assent to participate. Ethics approval was received from Institutional Review Board of the University of Oregon.

**Table 1 T1:** Inclusion and exclusion criteria at time of enrolment.

Inclusion criteria	Exclusion criteria
Female	Diagnosed with a developmental disability
10, 11, or 12 years old	Diagnosed with a psychotic disorder
Fluent in English	Diagnosed with a behavioral disorder, including autism
Normal or corrected-to-normal vision	Taking psychotropic medication other than stimulants
	MRI contraindications^1^
	Report or suspect being pregnant

^1^As described on the Lewis Center for Neuroimaging screening materials, including claustrophobia and presence of ferromagnetic material in the body.

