### Data Analysis

To determine the sample size for the study, Monte Carlo power analyses were performed in Mplus, with each analysis using 1,000 replications, and an expected attrition rate of 10% per wave. At the time of writing, attrition was only 6.0% between T1 and T2 and 3% between T2 and T3. With the chosen sample size standardized direct effects of 0.235 or larger and moderating effects of 0.15 or larger have at least 80% chance of being statistically significant. For mediation analyses, standardized indirect effects of 0.09 or larger have greater than an 80% chance of statistical significance (assuming the standardized direct effects are at least 0.30).

The majority of data collected as part of the study will be uploaded to the Research Domain Criteria database of the National Institute of Health and will be freely available to other researchers: https://nda.nih.gov/edit_collection.html?id=2315. This includes all imaging data, salivary hormone data, most questionnaires, K-SADS-PL interview data, IQ, and anthropometrics.

Exact procedures used for processing and analysis of the data will depend on the aims and subset of data used in specific empirical papers. Scripts applied to run analyses will be placed on Github: https://github.com/dsnlab/TAG_scripts. However, preprocessing of the imaging data will follow standard pipelines, using fmriprep for fMRI data, freesurfer for structural MRI data, and FSL for diffusion MRI data. The self-evaluation fMRI task will be analyzed as an event-related design, so that both condition (“self” versus “change”) and adjective type can be modeled. The self-disclosure fMRI task will also be analyzed as an event-related design, so that both statement depth (“superficial” versus “intimate”) and choice (to share or keep private) can be modeled. Any region-based analyses will be supplemented with whole-brain or network-based analyses. When conducting null hypothesis significance tests we set our statistical thresholds to at least p < .05 while correcting for multiple comparisons, although the precise approaches to do so might vary between empirical papers as standards in the field continue to evolve (e.g., joint magnitude-extent thresholds for fMRI are now recommended to be set at a minimum of p < .001 for magnitude).

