General analytic strategies will include latent growth curve models to examine correlated change among the variables of interest (aims 1, 2, and 3) and mediation models (aim 4). The growth curve models will compare linear and quadratic change over time and dual-process growth models will model relationships among variables of interest over time. Mediating effects will be assessed using mediation models appropriate for longitudinal data, which account for confounds such as trait-stability as well as wave-to-wave autocorrelation. To assess significance of indirect (mediated) effects, we will use bootstrap procedures to construct empirical standard errors to account for the skewed sampling distribution of the indirect path estimate. Where relevant and possible, we will examine the impact of demographic variables (such as gender identity or socioeconomic status) on the investigated associations by comparing models with and without these variables.

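### Bootstrap standard errors do not account for the skew of an indirect effect; a percentile bootstrap interval does, and the stated mediation power is not assured without it

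*Protocol article*

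**What the plan says.** The last paragraph of Data Analysis in the protocol article sets out how mediated effects will be judged significant: "we will use bootstrap procedures to construct empirical standard errors to account for the skewed sampling distribution of the indirect path estimate". It names no percentile or bias-corrected interval.

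The first paragraph of the same section gives the power for this aim: "standardized indirect effects of 0.09 or larger have greater than an 80% chance of statistical significance", with the condition "assuming the standardized direct effects are at least 0.30". The figure comes from Monte Carlo runs in Mplus with "an expected attrition rate of 10% per wave". The paragraph does not say which test of the indirect effect those runs used. It also does not say which direct effects the 0.30 refers to, or whether completers or all available data were analysed.

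**The concern.** An indirect effect is a product of two path coefficients, and its estimate has a skewed sampling distribution. The plan recognises this and turns to the bootstrap for that reason. The bootstrap deals with skew only if the shape of the resampled distribution is used, that is, its quantiles. Reducing it to a standard error discards the shape. The estimate divided by that standard error, or the estimate plus or minus 1.96 standard errors, again assumes a symmetric normal distribution.

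Aim 4 is the study's integrating hypothesis. A needlessly conservative test there means that true mediation is missed more often, although the same draws would support a better test. It also leaves open whether the power statement applies to the test that will be run.

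**Working it through.** **Inputs from the protocol article**

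- Sample: "leading to 174 participants at Time 1 of the study" (Participants). Data Analysis does not give the chosen sample size as a number, so 174 is taken.
- Planned attrition of 10% per wave: 174 × 0.9 × 0.9 = 140.9, about 141 at T3 (156.6, about 157, at T2).
- Observed attrition: "attrition was only 6.0% between T1 and T2 and 3% between T2 and T3", so 174 × 0.94 × 0.97 = 158.7, about 159.
- MRI at T2: 143 participants completed at least part (Timeline and Procedure). With 3% further loss, 143 × 0.97 = 138.7, about 139.
- Paths: a = b = 0.30, because 0.30 × 0.30 = 0.09.

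**Assumptions, not in the article:** one mediator, standardised normal variables, two-sided alpha 0.05, no multiplicity correction, direct path c′ of 0 or 0.30.

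**Step 1: check the sample size.** The plan also says "standardized direct effects of 0.235 or larger and moderating effects of 0.15 or larger have at least 80% chance of being statistically significant". By Fisher's z at n = 141, atanh(0.235) × √138 = 0.2395 × 11.75 = 2.81, and Φ(2.81 − 1.96) = 80.3%. At 157 and 174 the power would be 84.4% and 87.9%. This supports about 141 as the planned final sample.

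**Step 2: reproduce the mediation power.** Model: M = aX + e₁ with Var(e₁) = 1 − a² = 0.91. Y = bM + c′X + e₂ with Var(e₂) = 1 − (b² + c′² + 2abc′), which is 0.91 for c′ = 0 and 0.766 for c′ = 0.30. There were 2,000 to 6,000 replications with 1,000 resamples each (4,000 for the T2 MRI row below). Monte Carlo error is about 0.5 to 0.9 points. At n = 141 and c′ = 0, power is 80.0% for the delta-method (Sobel) test, 89.4% for joint significance of the two paths and 88.9% for the percentile interval. The stated figure is thus reproducible, but it cannot be traced to one test.

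**Step 3: is the skew handled?** The simulated estimate has skewness of about 0.5 to 0.6. At n = 141 and c′ = 0, against a nominal 2.5% on each side:

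| Interval | True value below it | True value above it |
|---|---|---|
| Estimate ± 1.96 bootstrap SE | 0.7% | 5.6% |
| Percentile bootstrap | 1.6% | 3.9% |

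The percentile interval reduces the imbalance but does not remove it.

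**Step 4: type I error at n = 141.** With a = 0 and b = 0.30, the bootstrap-SE test rejects 1.8% of the time and the percentile interval 4.9%. With the zero on the b path instead, the rates were 1.7–2.2% against 4.6–4.9%.

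**Step 5: power with a = b = 0.30**

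| Sample (a path / b path) | c′ | Bootstrap-SE test | Percentile interval | Difference (points) |
|---|---|---|---|---|
| 141 / 141, planned completers | 0 | 77.5% | 88.9% | 11.4 |
| 141 / 141 | 0.30 | 82.6% | 91.8% | 9.2 |
| 157 / 141, all available data | 0 | 80.2% | 91.2% | 11.0 |
| 157 / 141 | 0.30 | 85.7% | 94.5% | 8.8 |
| 143 / 139, T2 MRI mediator | 0 | 77.9% | 89.6% | 11.7 |
| 143 / 139 | 0.30 | 83.0% | 92.6% | 9.6 |
| 159 / 159, observed attrition | 0 | 84.5% | 92.9% | 8.4 |

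Repeat simulations of the first row gave 76% against 88–89%, a difference of 12 to 13 points. With no attrition (174, c′ = 0) the figures are 90.0% and 95.7%, so the loss shrinks as the sample grows.

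**The case against.** A reader might infer from the first row that the stated power above 80% is wrong. The article does not support that. Power falls below 80% only when c′ is 0 and the effective sample is about 141, and the article states neither c′ nor the test. The 0.30 condition can be read to include the direct path to the outcome, and then the bootstrap-SE test reaches 82–83%. With all available data at c′ = 0 it is about 80%, and at the observed attrition about 84%. The larger samples help less for a brain mediator measured at T2, where only 143 had MRI, but the dependence on c′ remains.

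The simulated model is also simpler than the planned one, which allows for trait stability and autocorrelation between waves. The power of those models cannot be computed from the article, so the figures show direction and rough size only.

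The plan nowhere writes out a z test or a symmetric interval, it leaves exact procedures to individual papers, and the authors may mean bootstrap confidence intervals. The choice of interval could reasonably be left to a fuller document if the article were silent. It is not silent: it names the standard error as the device that deals with skew, and on its plain reading that is incorrect.

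Finally, the error is conservative, so false claims of mediation are not inflated. That bears on severity and does not remove the point.

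**Conclusion.** The method point stands: a bootstrap standard error does not account for the skewed distribution of an indirect effect, and a percentile interval from the same draws largely would. In the plan's own case, at about 141 participants, the cost is a type I error of about 2% in place of 5% when one path is zero, and roughly 8 to 13 points of power. Power under the bootstrap-SE test is about 76–78% with c′ = 0 and 82–83% with c′ = 0.30, so the stated figure is not assured under this test but is not shown to be false.

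This rests on a single-mediator model with normal data, two-sided alpha 0.05 and no multiplicity correction. The plan also says "we set our statistical thresholds to at least p < .05 while correcting for multiple comparisons"; any such correction would lower power under either test. Severity is moderate: the stated method should be corrected, but no stated figure is clearly wrong and the error does not favour false positives.

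**What to change.** In the last paragraph of Data Analysis, state: *Indirect effects will be tested with percentile bootstrap 95% confidence intervals; an effect is significant when the interval excludes 0. Bootstrap standard errors are descriptive only.* The percentile form is preferable to the bias-corrected one here: in the run that compared them at n = 141 with a = 0 and b = 0.30, the bias-corrected interval rejected 8.2% of the time and the percentile interval 5.7%.

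In the first paragraph of Data Analysis, state which test of the indirect effect the mediation power figure refers to, and which direct effects are meant by the 0.30 condition.

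The first change costs one sentence and uses the same draws, with no new data. The second needs the record of the original Mplus runs or, if they used another test, a rerun of the simulation.

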## Discussion

Despite recent studies linking pubertal processes to brain development (6) and mental health outcomes (7), as well as those demonstrating the importance of brain developmental processes for adolescent mental health (85), there is limited knowledge on the pathways or mechanisms behind the development of mental illnesses such as depression and anxiety disorders in adolescence. The current study will provide a comprehensive picture of the pubertal, neurodevelopmental, and social psychological changes occurring during early-mid adolescence, and their relationship to the emergence of mental health problems, so that modifiable, developmentally specific risk factors can be identified as targets for early intervention and prevention efforts. The study focuses on female adolescents, because of the vast differences between the sexes in pubertal processes, as well as the increased prevalence of internalizing disorders in female adolescents (11).

The current study has several strengths:The use of a community-based sample allows for maximum generalizability to the population of female adolescents.The longitudinal design with three time points per participant provides more power (compared to the majority of published studies in the field, which have one or two time points), and allows for the exploration of nonlinear trajectories and of developmentally-specific risk predictions.The focus on social and self-perception processes such as self-evaluation, affiliation, and understanding of mental states better captures adolescent-specific changes and challenges than for example a focus on basic affective processing.The information collected is both comprehensive (e.g., by measurement of pubertal development that includes both hormonal and self-reported data, and by conducting multimodal neuroimaging) and spans several levels (biological, psychological, environmental). Thereby the data is suitable to apply mediation models and examine mechanisms predicting risk for mental illness.

Altogether, this study will help to understand the complex relationships between pubertal development, brain structure and connectivity, the behavioral and neural correlates of social and self-perception processes, and female adolescent mental health. The ultimate goal is to inform novel, developmentally targeted and biologically informed prevention and intervention services that leverage developmental plasticity to help all children, as well as those at higher risk, navigate the transition into and through adolescence with fewer mental health problems.

## Data Availability Statement

The imaging data, salivary hormone data, questionnaires, K-SADS-PL interview data, IQ, and anthropometrics generated as part of this study will be made available through the Research Domain Criteria (RDoC) database: https://nda.nih.gov/edit_collection.html?id=2315. Other data used and/or analyzed during the current study are available from the principal investigator (JP) on reasonable request.

## Ethics Statement

Ethics approval was received from Institutional Review Board of the University of Oregon. Parents/guardians give written informed consent and adolescents assent to participate, and this is repeated at every wave. Research staff have been trained in and follow protocols for confidentiality protection. Following Oregon state law, we have to break this confidentiality in case of non-accidental physical injury to the adolescent, or if we believe a person is in imminent danger of physical harm (including suicide). Risk assessment is done if the participant reports suicidal ideation, self-harm, or information indicating abuse. When risk assessment is done but breaking confidentiality is deemed unnecessary, we provide participants with resources for support.

